**FIGURE 2 clc23702-fig-0002:**
[figure not shown]
Study design ASA, acetylsalicylic acid; CKD, chronic kidney disease; CV, cardiovascular; MI, myocardial infarction; PAD, peripheral artery disease; PCI, percutaneous coronary intervention

### Study organizational structure

2.6

The study will be conducted by the sponsor (AstraZeneca) in collaboration with a contract research organization (Evidera), encompassing both cardiology and epidemiology expertise, with oversight from a scientific committee of cardiology experts external to both companies. The external scientific committee is responsible for: (i) The planning, development and scientific integrity of all publications and presentations derived from the ALETHEIA study in collaboration with AstraZeneca; (ii) The content and implementation of the study protocol and analysis plan, its interpretation, and reporting of the study results. All authors take responsibility for the veracity of the data. Full details of the study organization are provided in Table S2.

### Statistical analyses

2.7

Patient characteristics (as outlined in Figure 2) will be summarized at qualifying MI and at index date for patients treated with ticagrelor 60 mg, for the nonticagrelor P2Y_12_ inhibitor cohort, and for the non‐P2Y_12_ inhibitor cohort using descriptive statistics. All other statistical analyses will be performed among patients treated with ticagrelor 60 mg.

Persistence to treatment with ticagrelor 60 mg, including median time until discontinuation (if and when reached during follow‐up), and the percentage of patients remaining on treatment at specific timepoints from index date (Figure 2), will be calculated using the Kaplan–Meier (KM) method. Additionally, switches to another P2Y_12_ inhibitor or an anticoagulant will be similarly calculated.

The KM method will be used for calculating median times to clinical outcome events (if and when reached during follow‐up) and cumulative incidence at specific time points (Figure 2), presented along with 95% confidence intervals (CI). Incidence rates per 100 person‐years along with 95% CI will be calculated as the total number of patients with the event during follow‐up divided by the total person‐time at risk; during the intervals outlined in Figure 2. For events that can occur more than once, the all‐event rates (i.e., wherein patients are not censored at the occurrence of the event of interest) will also be calculated within the same intervals. Diagnoses for the same type of event recorded within 30 days will be assumed to be for follow‐up care, rather than a new event. For all outcomes, only timepoints at which a minimum of five events are recorded will be described.

Cox proportional hazards regression models will be used to assess the association of baseline patient characteristics (measured at index date) with the risk of the primary bleeding outcome, with the secondary CV composite outcome and with treatment discontinuation, respectively. Hazard ratios (HR) and 95% CIs will be presented.

The primary outcomes analyses will be based on an on‐treatment approach, censoring at treatment discontinuation. Additionally, an intention‐to‐treat approach will be used as a sensitivity analysis for the primary bleeding outcome and the secondary CV composite outcome. Sensitivity analyses will also be performed using two alternative definitions of treatment discontinuation, where the grace period is defined as 60 days in all databases, or where the discontinuation date is defined as the date of the last prescription of ticagrelor 60 mg plus half the number of days' supply in that last prescription plus 7 days.

Meta‐analyses will be applied to combine estimates derived from each country/database. Each meta‐analysis will be preceded by an assessment of heterogeneity in terms of patient characteristics and estimates. Heterogeneity will be quantified by the *I*
^2^‐statistic,^19^ and reasons for any observed heterogeneity will be explored prior to estimating the components of the meta‐analysis. A fixed‐effects approach will be used as the main method; random‐effects analyses will also be performed. The meta‐analysis results will be presented in Forest plots displaying the individual database‐level estimates with corresponding 95% CIs.

Regression models combined in the meta‐analyses will use predefined sets of covariates. These covariates will be selected based on the results of the country‐level regression models and clinical knowledge.

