### Clinical outcomes

2.5

Study measures, including outcomes, are defined using diagnosis, procedure, and medication codes in the formats used in each database; full definitions are presented in Table S1.

To ensure sufficient precision, clinical outcomes for all study populations will only be analyzed if the a priori threshold of 5000 person‐years on‐treatment with ticagrelor 60 mg is met in the Primary population, as a total across all data sources.

The primary outcome, bleeding requiring hospitalization, is defined as an inpatient admission with at least one overnight stay with a primary diagnosis of bleeding. In a sensitivity analysis, the primary bleeding outcome is defined as bleeding events associated with an inpatient admission of ≥2 overnight stays. Additional bleeding outcomes include the individual components of the primary outcome (hospitalization for intracranial hemorrhage, gastrointestinal bleeding and other bleeding, respectively), bleeding episodes not requiring hospitalization, and fatal bleeding.

Outcomes were identified on the event date recorded in the EHD; for composite outcomes, the earliest date of any of the components was used to define the event date. The secondary CV composite outcome is defined as the composite of hospitalization for MI or stroke, and all‐cause mortality. Additional outcomes include the individual components of the secondary CV composite outcome, three‐point MACE (composite of hospitalization for MI or stroke, and CV death), hospitalization for ischemic stroke, CV death, as well as coronary heart disease (CHD) death. To ensure harmonized definitions across all databases, fatal bleeding, CHD death, and CV disease (CVD) death are defined as death within 28 days of an inpatient hospital admission with a primary diagnosis of bleeding, CHD, and CVD, respectively. Sensitivity analyses for these outcomes will be performed in databases reporting cause of death from death certificates (UK and Sweden). Exploratory outcomes include dyspnea and lower‐limb amputation, as well as bleeding requiring transfusion (only available in the US databases).

Due to insufficiently detailed clinical data in all databases to adequately adjust for imbalances in clinical characteristics between cohorts for comparative analyses, clinical outcomes will only be analyzed in the ticagrelor 60 mg cohorts (i.e., not in the reference cohorts).

Subgroup analyses of interest are described in Figure 2.

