### Sample size estimation

2.8

No power calculations were performed as all objectives are descriptive in nature. The a priori threshold of 5000 person‐years on‐treatment for outcomes analyses among patients treated with ticagrelor 60 mg was based on an assumed event rate for bleeding requiring hospitalization of 0.5 per 100 person‐years (the annualized major bleeding rate was approximately 0.9% in the PEGASUS‐TIMI 54 trial).^17^ With a sample size of 5000 patients (assuming an average of 1 year on treatment), the 95% CI would be 0.3–0.7 events per 100 person‐years. The event rate for MACE (hospitalization for MI, stroke, or CV death) was expected to be approximately 2.5 per 100 person‐years (the annualized rate for this outcome was approximately 2.7% in the PEGASUS‐TIMI 54 trial).^17^, ^20^ Given that this outcome is expected to occur more frequently than bleeding requiring hospitalization, the threshold of 5000 person‐years will be applied for all clinical outcome analyses.

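### The 0.3–0.7 precision figure is for one summed sample, but the main method pools sparse database-level rates and need not deliver it

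*Protocol article*

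**What the plan says.** Protocol article, section 2.8 (Sample size estimation), starts from an "assumed event rate for bleeding requiring hospitalization of 0.5 per 100 person‐years" and 5000 patients treated for one year on average, and concludes that "the 95% CI would be 0.3–0.7 events per 100 person‐years". Section 2.5 (Clinical outcomes) uses this as a gate: clinical outcomes are analyzed only if the 5000 person-year threshold "is met in the Primary population, as a total across all data sources".

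Section 2.7 (Statistical analyses) then describes a different calculation. Meta-analyses "will be applied to combine estimates derived from each country/database", and a fixed-effects "approach will be used as the main method". Random-effects analyses are run alongside, I² is assessed beforehand, and forest plots show each database's own estimate and interval. The same section says that, for all outcomes, "only timepoints at which a minimum of five events are recorded will be described". The article gives no pooling scale, no weights and no handling of zero events. It also does not say whether the five-event count is taken per database or over all databases.

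**The concern.** The precision statement and the main method belong to different estimators. The interval treats all databases as one Poisson count. The meta-analysis first estimates a rate in each of seven databases and then averages those rates. With large counts the two agree. With a handful of events per database they do not, because the usual inverse-variance weights are computed from the same counts as the rates, so chance highs or lows are over-weighted.

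Bleeding requiring hospitalization is the primary outcome, and the gate exists to guarantee a precise estimate of it. If the pooled rate is off by a tenth or a quarter and its interval under-covers, meeting 5000 person-years does not secure what the gate is meant to secure. The individual bleeding components have fewer events than the total, so they are more exposed.

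**Working it through.** **Inputs.** Rate 0.5 per 100 person-years and 5000 person-years (section 2.8). Projected patients (Table 3): Medicare 3100, MarketScan 1200, Italy 1000, Sweden 800, Optum 750, UK 250, Germany 150; total 7250. Upper rate for sensitivity: about 0.9% per year, the major bleeding rate in the cited ticagrelor trial (section 2.8). Assumptions: person-time proportional to projected patients, the same true rate everywhere, and events counted over all follow-up. The section 2.7 rates are also reported by interval, where counts would be lower.

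**Step 1: reproduce the stated interval.** Events = 0.005 × 5000 = 25. Standard error = √25 / 5000 = 0.001, or 0.1 per 100 person-years. Interval = 0.5 ± 1.96 × 0.1 = 0.304 to 0.696, which matches. The exact Poisson interval is 0.32–0.74.

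**Step 2: split the 25 events.** Expected events = 0.005 × 5000 × n / 7250.

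| Database | Person-years | Expected events | P(at least 5) |
|---|---|---|---|
| Medicare | 2138 | 10.7 | 98% |
| MarketScan | 828 | 4.1 | 40% |
| Italy | 690 | 3.4 | 27% |
| Sweden | 552 | 2.8 | 15% |
| Optum | 517 | 2.6 | 12% |
| UK | 172 | 0.9 | 0.2% |
| Germany | 103 | 0.5 | <0.1% |

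The chance of no events is 42% in the UK and 60% in Germany. The chance that at least one of the seven has none is 81%.

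**Step 3: why inverse-variance pooling drifts.** Let database i have d events in T person-years.

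- Log scale: variance about 1/d, so the weight is d. The pooled rate is exp[Σ d·log(d/T) / Σ d]. By the log-sum inequality this is never below Σd/ΣT.
- Raw scale: variance d/T², so the weight is T²/d. The pooled rate is ΣT / Σ(T²/d). With all counts positive, the Cauchy–Schwarz inequality shows that it never exceeds Σd/ΣT.
- At d = 0 the log rate and the raw weight are both undefined, so a correction or an exclusion is needed.

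**Step 4: size.** 200,000 simulated data sets at 5000 person-years, true rate 0.50 per 100 person-years in every database:

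| Method | Mean | Bias | Mean 95% interval | Coverage |
|---|---|---|---|---|
| Total events / total person-years | 0.500 | 0% | 0.305–0.695 | 94.8% |
| Log, 0.5 for zeros | 0.563 | +13% | 0.38–0.83 | 91% |
| Log, 0.5 added to all | 0.625 | +25% | 0.43–0.90 | 78% |
| Log, zeros dropped | 0.571 | +14% | 0.39–0.85 | 90% |
| Log, under five dropped | 0.599 | +20% | 0.37–0.99 | 88% |
| Raw, 0.5 for zeros | 0.412 | −18% | 0.24–0.59 | 73% |
| Raw, zeros dropped | 0.443 | −11% | 0.26–0.63 | 84% |
| Raw, under five dropped | 0.548 | +10% | 0.27–0.83 | 95% |
| Square root, all kept | 0.458 | −8% | 0.29–0.66 | 90% |

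Both extremes, −18% and +25%, come from variants that do not use the five-event rule. Where databases under five are dropped, on average 1.9 of 7 databases and 2753 of 5000 person-years (55%) remain.

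**Step 5: more favorable inputs.** Bias range over the same eight variants:

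- 7250 person-years, rate 0.5: −14% to +17%.
- 5000 person-years, rate 0.9: −12% to +14%.
- 7250 person-years, rate 0.9: −9% to +10%.

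**The case against.** The strongest reply is that the article never commits to inverse-variance weights. It says only that the approach is fixed-effects, and a common-rate Poisson model also fits that description and shows no bias. Scale and zero handling are details that a condensed article may leave to the full analysis plan. This stands, and it limits the severity. It does not remove the mismatch, because combining database-level estimates, with I² and forest plots, ordinarily means a two-stage inverse-variance analysis, and the stated precision was not derived for that.

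A reader might infer that the five-event rule drops small databases, so that the pooled rate is necessarily selected upward. The text does not support this. The rule limits which timepoints are described, and nothing there excludes a database from the meta-analysis. The 0.60 mean and 88% coverage are conditional on that use.

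A reader might also infer that only Medicare will reach five events. That is true of expected counts at 5000 person-years, but Medicare is alone in only 33% of simulations. At one year for each of 7250 patients, MarketScan (6.0) and Italy (5.0) also reach five. At 0.9 per 100 person-years as well, five databases exceed it.

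The interval is also fairly called a planning approximation in a descriptive study, and it is correct for the total on which the gate is counted. The random-effects analyses, the heterogeneity assessment and the analysis without Optum and MarketScan are sensible, but none addresses sparse counts.

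**Conclusion.** The point holds as a mismatch between the precision claimed and the main method named. At the planning figures, every ordinary inverse-variance variant tried was biased, by about −18% to +25%, and seven of the eight had 95% intervals covering only 73–91%. The eighth kept 95% coverage, but its rate was 10% too high and its mean interval widened to 0.27–0.83. The bias shrinks with more person-time or a higher rate but does not vanish in the range checked.

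Its direction and size cannot be fixed from the article, since they depend on unstated choices, and a count-based model would remove it. The figures rest on person-time proportional to the Table 3 projections and a common true rate. This should be corrected, but it falls short of a must-fix because the analysis plan, which is not shown, may already specify pooling on counts.

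**What to change.** For event rates:

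- Have every database contribute event counts and person-years, zeros included. Take total events over total person-years with an exact Poisson interval as the fixed-effect estimate, and a Poisson model with a random database intercept as the random-effects version.
- State that the five-event minimum governs display only, never entry into pooling, and whether it is counted per database or overall.
- State in section 2.8 that 0.3–0.7 refers to the summed-count estimator. The exact interval, 0.32–0.74, rounds to the same figures.

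This does not cover hazard ratios or Kaplan–Meier estimates, whose pooling was not examined here. The cost is a small change to the analysis and its wording, with no new data. One practical condition is that data holders must be able to contribute small counts to a combined total. Their release rules are not in the documents and need to be checked.

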### Sample size estimation

2.8

No power calculations were performed as all objectives are descriptive in nature. The a priori threshold of 5000 person‐years on‐treatment for outcomes analyses among patients treated with ticagrelor 60 mg was based on an assumed event rate for bleeding requiring hospitalization of 0.5 per 100 person‐years (the annualized major bleeding rate was approximately 0.9% in the PEGASUS‐TIMI 54 trial).^17^ With a sample size of 5000 patients (assuming an average of 1 year on treatment), the 95% CI would be 0.3–0.7 events per 100 person‐years. The event rate for MACE (hospitalization for MI, stroke, or CV death) was expected to be approximately 2.5 per 100 person‐years (the annualized rate for this outcome was approximately 2.7% in the PEGASUS‐TIMI 54 trial).^17^, ^20^ Given that this outcome is expected to occur more frequently than bleeding requiring hospitalization, the threshold of 5000 person‐years will be applied for all clinical outcome analyses.

### Ethical considerations

2.9

This observational study will be performed in accordance with ethical principles consistent with the Declaration of Helsinki and the International Society for Pharmacoepidemiology guidelines on Good Pharmacoepidemiology Practice. The final protocol has been approved by Ethics Committees/Institutional Review Boards, as applicable in each of the countries.

This study does not involve any primary data collection; hence, subject informed consent is not applicable.

## DISCUSSION

3

ALETHEIA aims to enhance the understanding of patient characteristics, treatment patterns, and bleeding and CV outcomes in patients with a history of MI on extended DAPT with ticagrelor 60 mg in routine clinical practice. The study will include patient‐level data from seven observational EHD sources from five countries across Europe and the US, to obtain a large and geographically diverse patient sample. The main study populations are defined to align, as much as possible in observational EHD, with the overall PEGASUS‐TIMI 54 population (the Primary population)^6^ and its subgroup relevant to geographic adaptations of the ticagrelor 60 mg label (the Secondary population, aligned with the European label).^17^, ^18^ Given the lack of robust data on ticagrelor 60 mg use in routine clinical practice, ALETHEIA is therefore designed to supplement and further explore clinical trial findings by generating information that may be used to guide appropriate patient selection for this therapy.

The stepwise design with an a priori threshold of person‐years on treatment has been implemented to ensure that precise estimates of clinical outcomes can be calculated, to more accurately inform clinical decision‐making.

Data from routine clinical practice on prescription patterns and clinical outcomes in patients treated with ticagrelor 60 mg post‐MI are very limited. In a recent observational study in 181 patients in Italy, including those with a previous MI treated with ticagrelor 60 mg twice daily plus aspirin, the 1‐year risk of MACE was 5.0%, with MI being the main contributor (3.9%), while no major bleeding events occurred.^11^

Based on the TWILIGHT trial^21^ findings and latest updates to clinical guidelines,^8^ monotherapy with a P2Y_12_ inhibitor is an emerging treatment strategy for patients post‐percutaneous coronary intervention. In this study, all patients are assumed to be on concomitant ASA, since data on medications that can be purchased without a prescription, such as ASA, are not available in all countries. Based on the product labels and the time period in which the observations the ALETHEIA study took place (most patients pre‐2019), concomitant use of ASA is a reasonable assumption. The extent of concomitant ASA use will be described in databases capturing this data, to assess consistency with this assumption.

One strength of this study is that patient characteristics will also be described among patients treated with a nonticagrelor P2Y_12_ inhibitor and those who are not treated with any P2Y_12_ inhibitor, at a comparable time from their MI to patients initiating ticagrelor 60 mg. This will provide useful contextualization of the findings, as patient characteristics (e.g., risk factors, disease severity, comedications), prescriber preferences, and local guidelines may influence the selection of treatments prescribed in clinical practice. The main reasons for not performing comparative outcomes analyses include the expected lack of complete information on all covariates assumed to be needed to adequately balance the populations for baseline risk, leading to potential residual confounding, as well as key methodological challenges for comparative analyses, such as determining use of low‐dose ASA, which is not captured in all databases. While the data are physician‐reported and the claims data are adjudicated for reimbursement purposes, no additional adjudication of clinical events is performed, a limitation shared with most observational database studies. However, some databases used in the study (e.g., the Swedish National Inpatient Register) have been validated for clinical diagnoses, including CV disease.^22^, ^23^

The study also has a number of limitations typical of multi‐country, register‐based, observational studies. First, while the data sources used in this study reflect routine clinical practice, they are not primarily established for research purposes. Therefore, coding practices of diagnoses and medications (e.g., prescriptions issued vs. filled) may vary between databases. While study definitions have been harmonized across databases and based on validated algorithms wherever possible,^22^ these differences may influence the ascertainment of patients for inclusion in the study and of clinical outcomes. Second, characteristics and baseline risks may differ between countries due to differences in patient characteristics, healthcare systems, prescribing practices, and other population‐level factors. This may limit our ability to conduct meta‐analyses, as well as the generalizability of the study findings, but this limitation is offset by the advantages of using multiple databases, which includes increased geographical representativeness and sample size. In this study, analyses are harmonized using common definitions across the databases. Additionally, sensitivity analyses (e.g., around prescription length) and the calculation of the *I*
^2^‐statistic for meta‐analyses intends to mitigate and quantify heterogeneity across databases. While outcomes based on cause of death will be defined using the same definition across all databases to ensure harmonization, the contextualization of these findings with sensitivity analyses using data from death certificates (available from UK and Sweden) will be a valuable contribution in advancing methodology in observational studies. Third, the European databases included in this study do not contain comprehensive information on blood transfusions, so major bleeding events are primarily defined using only inpatient diagnostic codes for bleeding. Still, an exploratory outcome on bleeding requiring transfusions will be assessed in the US databases, where transfusion procedures are expected to be more reliably captured. Furthermore, common bleeding definitions used in randomized trials require laboratory parameters to categorize bleeding events, but as this information is not consistently available from EHD sources, bleeding scales were not used in in ALETHEIA. Since comprehensive information on mortality is available in US Medicare claims but not in Optum Clinformatics and IBM MarketScan, additional meta‐analyses of outcomes, whether or not these outcomes include death, will be performed as a sensitivity analysis in a restricted study population, excluding patients from the Optum and MarketScan databases. The rationale is to provide results for both the bleeding and CV outcomes in populations with similar age distributions.

Fourth, the 5000 person‐years on treatment threshold is considered as the minimum number required for sufficient precision in clinical outcome assessment. While this threshold is expected to be met, person‐years on treatment is a function of both time on treatment and number of patients, and is thereby influenced by the databases' available duration of longitudinal data as well as their national coverage.

Fifth, to allow contextualization of patient characteristics, reference cohorts of nonticagrelor patients will be described at a similar time point from their qualifying MI as will be observed among the patients initiating ticagrelor 60 mg. In routine clinical practice, patients treated for ACS may continue being prescribed a P2Y_12_ inhibitor more than 12 months after an MI, despite not being intended for extended antiplatelet treatment. To limit the inclusion of such patients in the nonticagrelor P2Y_12_ inhibitor cohort, categorization of patients into either reference cohort will be based on their treatment at a minimum of 15 months after their qualifying MI. Exposure to nonticagrelor P2Y_12_ inhibitors or lack of exposure to P2Y_12_ inhibitors may therefore be assessed after the index date for some patients, introducing a survival bias to patients in the reference cohort. Although the extent of this bias cannot be quantified a priori, the impact is likely minimal given the short maximum timeframe between the index date (≥12 months post‐MI) and the time of treatment assessment (≥15 months post‐MI). Sixth, while the primary analyses will be conducted using an on‐treatment approach, reflecting events that occur when patients are receiving ticagrelor 60 mg, censoring at treatment discontinuation may introduce bias due to informative censoring. This could occur if the risk of discontinuing treatment is related to the events of interest, thus violating the key assumption in survival analyses that censoring events are random. While difficult to properly account for, the likelihood of such bias being introduced will be assessed by investigating baseline factors associated with discontinuation. To further assess the potential risk of informative bias, event rates will also be calculated using an intention‐to‐treat approach.

In conclusion, despite the increasing recognition of observational studies to inform healthcare decision‐making, knowledge about treatment patterns and associated outcomes in patients treated with ticagrelor 60 mg in routine clinical practice is limited. The multi‐country, observational ALETHEIA study is designed to address this gap. The study objectives and the a priori specified stepwise approach used for outcomes analyses are expected to generate useful insights for clinical decision‐making and treatment optimization.

